**7.4.6.5. HIV Screening**

Subjects with an active HIV infection are excluded from the study. Prior HIV screening results obtained as standard of care for allo-HSCT confirming the subject is HIV-negative may be used for determining eligibility, and tests do not need to be repeated. Subjects whose HIV status is unknown must have results confirming negative status before enrollment.

## 7.5. Efficacy Assessments

Assessments will be performed at three stages: 1) prior-treatment screening to assess the inclusion and exclusion criteria (once from days -7 to -1 before medication); 2) treatment evaluation to determine the response and adjustment of medication maintenance (twice weekly for week 1, once weekly from week 2 to 6, once every 2 weeks from week 7 to 12, and once every month from week 13 to 24 after the start of medication n); 3) post-treatment evaluation for follow-up (every 2 months for 6 months).

### 7.5.1. GVHD Staging and Grading

Acute GVHD grading will be performed by the investigator on a weekly basis for the first 8 weeks after randomization, then every 28 days thereafter. GVHD staging and grading will also occur on Days 100, 180, and 365 and at the EOT visit.

On-treatment acute GVHD grading should be performed relative to the Day 1 assessment.

If subjects withdrew due to reasons other than GVHD progression, then GVHD staging and grading will be assessed at the safety follow-up visit and every 28 days thereafter during survival follow-up until progression of GVHD, start of new anti-GVHD therapy, or death.

Data regarding the quantification of acute GVHD symptoms (extent of skin rash, total bilirubin level, volume of diarrhea) should be reported using MAGIC guidelines ^[19]^; response will be assessed as per CIBMTR modifications to the IBMTR response index.

- Skin:
- Only areas involved with active erythema should be used for determination of body surface area staging based on the rule of nines.
- A portion of a body area segment may be used for the quantification.
- Desquamation or fluid-filled bullae should be reported if present, as these findings are the hallmark of Stage 4 skin GVHD.
- Liver:
- Liver GVHD staging is based solely on total (not conjugated/direct) serum bilirubin levels.
- Liver GVHD manifesting as transaminitis without concomitant elevation in serum bilirubin should be diagnosed when the presence of GVHD is confirmed by liver biopsy (where appropriate) and score it as Stage 0.
- If bilirubin levels were elevated before the diagnosis of GVHD in another target organ and do not increase further, liver GVHD should not be diagnosed in the absence of biopsy confirmation. However, if hyperbilirubinemia develops at the same time or after the onset of GVHD in another target organ, liver GVHD is presumed to be present in the absence of an identified alternative cause.
- Upper GI:
- Symptoms of concern for upper GI GVHD include anorexia, nausea, vomiting, and dyspepsia, and assessment depends on close attention to caloric intake and symptom reporting.
- An upper GI endoscopy should be performed whenever possible to confirm upper GI GVHD; however, the diagnosis may be made without biopsy confirmation.
- GVHD is typically not considered as a possible etiology when nausea lasts fewer than 3 days, or with fewer than 2 vomiting episodes per day for at least 2 days, or anorexia without weight loss.
- Lower GI:
- Staging of lower GI GVHD relies on accurate measurement of daily stool volumes and documentation of the presence of hematochezia or severe abdominal pain.
- In cases where stool volume cannot be closely measured, volume should be calculated based on average of 200 mL per episode multiplied by the number of episodes in a 24-hour period.
- At the time of GVHD onset, staging should be based on the highest daily volume during the 3 days before diagnosis (excluding volumes attributable to procedures such as bowel preps or endoscopy).
- After the initiation of treatment, lower GVHD staging should be based on the diarrhea volume using the following measurements (in the order of preference): 1) average of 3 consecutive days, 2) average of 2 consecutive days, or 3) the volume on day of assessment.
- Severe abdominal pain, ileus, and/or grossly bloody stool should be documented when present because Stage 4 lower GI GVHD is staged based on the presence of these symptoms and is independent of volume of diarrhea.

### 7.5.2. Chronic GVHD Assessment

Subjects will be assessed for signs and symptoms of cGVHD according to local institutional practice at screening, during the treatment phase, at the end of treatment, and during re-treatment (if applicable). Definitive and possible manifestations of cGVHD should be assessed as per NIH consensus guidelines for cGVHD^[32]^.

### 7.5.3. Graft Failure and Donor Chimerism

Monitoring of graft failure will be primarily based on the monitoring of blood counts with subsequent confirmation by chimerism studies, as clinically indicated. Donor chimerism after a HSCT involves identifying the genetic profiles of the recipient and of the donor and then evaluating the ratio of donor to recipient cells in the recipient’s blood, bone marrow, or other tissue. Chimerism testing using peripheral blood or bone marrow will be performed at the treating investigator’s discretion according to local institutional practice. In general. Genomic polymorphisms should be assessed via polymerase chain reaction analysis of short tandem repeat loci from isolated lymphocytes or myeloid cells. Fluorescence in situ hybridization analysis may also be used in cases with sex-mismatched transplants. If a subject experiences graft failure (ie, initial blood or marrow donor chimerism > 5% declining to < 5% on subsequent measurements), any action taken, including rapid taper of immunosuppression, administration of nonscheduled donor lymphocyte infusion, stem cell boost or other intervention(s), should be recorded on the appropriate eCRF.

### 7.5.4. Post-Transplant Lymphoproliferative Disorder Assessment

Staining for Epstein-Barr virus for PTLD testing will be performed according to local institutional practice at the treating investigator’s discretion.

### 7.5.5. Relapse/Recurrence of Underlying Hematologic Disease

Subjects will be followed for relapse or recurrence of their underlying hemotologic disease as per institutional standards during treatment and follow-up. Details on hematologic disease relapse will be recorded on the appropriate eCRF.

New malignancies should be reported as separate AEs.

## 7.6. Blood Sample Collection

Blood samples for GVHD biomarkers will be obtained at acute GVHD onset for all subjects. Then, the subjects will be randomized to receive one of the two treatments according to the risk of acute GVHD.

# 8. STATISTICS

## 8.1. Selection of Sample Size

The sample size is calculated according to the primary endpoint (ORR) of the study. Based on our published phase I study of 32 acute GVHD patients who received steroids as first-line therapy, an expected proportion of 55% for the patients treated with corticosteroids only was established ^[4]^. Based on our published data of patients with acute GVHD grade I–IV who received steroid-ruxolitinib (5 mg/day) as first-line therapy, the ORR was 82.05% ^[24]^. Patients with acute GVHD grade I were also included in the phase I analysis. Thus, an expected proportion of 75% for the patients treated with steroid-ruxolitinib (5mg/day) was established. This study is planned to detect a response difference between treatment arms at a two-sided significance level α=5% with a power of 1-β=80%. The sample size was estimated using PASS software based on the primary endpoint (ORR). The calculated sample size is shown in Figure 1 (N1=99, N2=99); allowing a withdrawal rate of 10%, 198 patients (99/group) will be required.

## 8.2. Level of Significance

The 1-sided significance level for the primary and key secondary endpoint analysis is 0.025. The 2-sided significance level for other analyses is 0.05. All CIs will be 95%.

## 8.3. Statistical Analyses

### 8.3.1. Primary Analyses

The baseline characteristics of patients will be reported in detail. The discrete variables are described by a median with IQR. The mean and standard deviation (SD) is used for quantitative variables. A logistic regression model is established as the primary study endpoint of GVHD treatment, as described above. In this model, the treatment grouping factor (ruxolitinib plus corticosteroids vs. corticosteroids alone), stratified variables of acute GVHD risk (high-risk vs. intermediate risk), and disease status before transplantation (complete remission vs. non- complete-remission) are included as covariates. The subgroup analysis is based on the significant effect of biomarker risk stratification on survival outcomes.

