## 1.2. MAGIC Algorithm Probability

The clinical stage of acute GVHD is defined according to each involved organ’s clinical assessment of symptoms. The organ stages are totaled in an overall grade (I–IV) ^[16]^. Grade III/IV acute GVHD is associated with high mortality rate (50%–70%) and the possibility of steroid resistance. Serum biomarkers have also emerged as an additional potential measurement of acute GVHD severity ^[17, 18]^. The Mount Sinai Acute GVHD International Consortium (MAGIC) is a group of 25 stem cell transplantation centers conducting GVHD research. It has established an algorithm that combines two biomarkers, namely ST2 and REG3α. The MAGIC algorithm probability (MAP) predicts the response to first-line treatment of corticosteroids and 6-month non-relapse mortality (NRM). When measured at acute GVHD onset, the MAP could categorize the patients into three risk groups, each group with significantly different risk of NRM. The proportion of patients resistant to treatment at week 4 was higher in the high MAP risk group than in the low-risk group (67% vs. 30%, p = 0.03) ^[14, 19]^. Therefore, novel and active first-line therapies are urgently required in patients with high-risk acute GVHD prone to steroid resistance ^[9, 20]^.

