## 4.3. GVHD biomarker Luminex assays

Peripheral blood samples are collected at acute GVHD onset ^[17, 28, 29]^. Designated personnel are responsible for collecting and transporting these blood samples that are shipped to Bofurui Biolab for MAP analyses for ST2 and REG3a by flow cytometry. Luminex Assay Human Premixed Multi-Analyte Kits (R&D, MN, USA, Catalog No. LXSAHM-05) is used for measurement of ST2 and REG3a, according to the manufacturer’s protocol. Samples (diluted as 1:2) and standards are run in duplicate, the absorbance is measured (Luminex 200), the data are estimated using versionXponent_4.2 (Luminex 200), and MAP is calculated accordingly.

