### 7.2.2. Disease Characteristics and Treatment History

A disease-targeted medical and medication history including hematologic malignancy type, current GVHD staging, date of diagnosis, sites of disease, prior anticancer therapy, ablation therapy, prophylaxis therapy, donor type, and other details related to the disease under study will be collected at screening.

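### The Day-28 ORR logistic model in 8.3.1 uses MAP and clinical severity only through one high/intermediate cut, forgoing a possible gain in precision; the planned 80% power is kept.

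*Protocol*

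**What the plan says.** Section 8.3.1 names a logistic regression for the primary endpoint. Its terms are treatment arm and the "stratified variables of acute GVHD risk (high-risk vs. intermediate risk), and disease status before transplantation". Section 4.4 shows that these are exactly the two factors that stratify the randomisation. No other baseline covariate is listed.

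The Synopsis lists the same covariates but gives the model a different role. There, ORR is compared by the stratified CMH test, and the logistic model is an additional, exploratory analysis.

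On the variables left out in their full form:

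- **MAP and response.** Section 1.2 says MAP predicts response to first-line corticosteroids. It reports that the proportion "resistant to treatment at week 4 was higher in the high MAP risk group than in the low-risk group" (67% vs 30%). The same section ties grade III/IV to possible steroid resistance.
- **MAP availability.** Section 7.6 takes the onset sample in all subjects, ahead of randomisation. Section 4.3 says ST2 and REG3α are measured "and MAP is calculated accordingly".
- **Grade availability.** Section 7.2.2 collects "current GVHD staging" at screening, and 7.5.1 grades on-treatment GVHD against the Day 1 assessment.
- **What the risk factor contains.** Section 3.1 defines intermediate or high risk by the Minnesota score and the MAGIC biomarker algorithm together. Low-risk patients are not eligible.

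For the sample size, 8.1 states a "two-sided significance level α=5% with a power of 1-β=80" per cent. For control, "an expected proportion of 55% for the patients treated with corticosteroids only was established". For the experimental arm, "an expected proportion of 75% for the patients treated with steroid-ruxolitinib (5mg/day) was established". With 10% withdrawal this gives 99 per group.

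**The concern.** The protocol identifies two baseline measures as related to its own primary endpoint and obtains both before treatment. The model for that endpoint then keeps only a two-level summary of them. Differences in MAP or grade between patients in the same risk stratum stay in the unexplained variation.

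Two things are at stake. The first is precision: in a logistic model, adding a truly prognostic baseline term raises the power of the treatment test for a given marginal difference. The second is interpretation: a chance imbalance between arms in MAP or grade, within a risk stratum, cannot be corrected by the stated model. It does not inflate the type I error over repeated trials, but it can make the one observed result harder to read.

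**Working it through.** **1. The plan's own figure.** Inputs from 8.1: p0 = 0.55, p1 = 0.75, two-sided α = 0.05, power 80%, withdrawal 10%. Section 8.2 says "The 1-sided significance level for the primary and key secondary endpoint analysis is 0.025", which gives the same critical value, 1.96.

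Pooled-variance formula without continuity correction, mean proportion 0.65:

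n = [1.96·√(2·0.65·0.35) + 0.8416·√(0.55·0.45 + 0.75·0.25)]² / 0.20²
= [1.322 + 0.555]² / 0.04 ≈ 88.1, so 89 per arm.

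89 / 0.9 = 98.9, so 99 per arm and 198 in total. This matches the protocol, and no covariate enters the calculation. Unadjusted power is 80.4% at 89 per arm and 84.4% at 99.

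**2. What the 67% vs 30% contrast gives.** Odds ratio = (0.67/0.33)/(0.30/0.70) = 4.74, log odds ratio 1.56. This compares high with low MAP. The trial excludes low-risk patients and the model already separates high from intermediate, so the figure does not give the residual effect of MAP within a stratum. The grade statement carries no number for response. The residual effects must be assumed.

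**3. Power with and without the two terms.** Simulation of 5,000 trials per scenario, 89 evaluable per arm, marginal ORR held at 55% vs 75%, Wald test at 1.96. Assumptions: 50% high risk (log OR 0.6 against response), 30% not in remission (log OR 0.2), 40% grade III–IV, and MAP standardised and independent of the strata and of grade. The residual log OR is per SD of MAP and, equally, for grade III–IV.

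| Residual log OR | Stated model | Plus MAP and grade | Gain (points) |
|---|---|---|---|
| 0 | 80.7% | 80.7% | 0 |
| 0.25 | 81.2% | 81.8% | 0.6 |
| 0.4 | 80.9% | 82.3% | 1.4 |
| 0.6 | 81.2% | 84.0% | 2.8 |
| 0.8 | 80.9% | 86.0% | 5.1 |
| 1.0 | 80.8% | 88.8% | 8.0 |

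- An extreme bound, with the full 1.56 per SD of MAP and no grade effect, gives 79.9% then 90.9%.
- At 99 per arm the pairs are 85.1% and 86.3% (log OR 0.4), and 84.5% and 88.8% (log OR 0.8).
- With no treatment effect (residual log OR 0.6), rejection is 4.7% for the stated model and 4.6% for the extended one.

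A second set of assumptions was run with 4,000 trials per scenario: 40% high risk with OR 0.5, OR 0.75 to 0.5 per SD of MAP within stratum, OR 0.7 to 0.5 for grade III–IV. At 89 per arm it gives 81–83% for the stated model and 82–85% with the added terms. At 99 per arm it gives 85–86% and 86–89%. The gain is 0 to 4 points.

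**4. Chance imbalance.** With 89 per arm, a difference of 1.96 standard errors in mean MAP is 1.96·√(2/89) = 0.29 SD. At an assumed OR of 0.75 to 0.5 per SD (log OR 0.29 to 0.69) this moves the log odds by 0.08 to 0.20. The planned effect is ln[(0.75/0.25)/(0.55/0.45)] = 0.90. Such an imbalance would therefore be worth about 9% to 23% of it.

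**5. Room for the terms.** Expected non-responders: 89·(0.45 + 0.25) ≈ 62 of 178 evaluable, or 99·0.70 ≈ 69 of 198. For five model terms, 62 leaves about 12 per term.

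**The case against.** Adjusting for exactly the stratification factors is a sound and conventional choice, and nothing in 8.3.1 is an arithmetical error. That stands.

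A reader might infer that the omission costs the trial power it was promised. The documents do not support this: 99 per arm comes from an unadjusted calculation, and the stated model delivers about 80–81% at 89 per arm in every scenario of the table. A reader might also take 67% vs 30% as the size of the lost information. That contrast involves a group the trial does not enrol, and the risk factor already absorbs part of MAP and of clinical severity. How much independent information remains is unknown and could be near zero.

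The Synopsis is a further limit. If the stratified CMH test is the ORR comparison and the logistic model only explores, extra logistic terms leave the primary test unchanged. This narrows the point without removing it, because 8.3.1 is the section on primary analyses and names the logistic model.

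The Synopsis also describes analyses in the past tense, including post hoc subgroups by biomarker risk and GVHD grade. If the outcomes had been seen when that was written, new covariates could no longer count as prespecified. The protocol does not settle this.

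**Conclusion.** The point holds as a modest efficiency recommendation. The model uses MAP and severity only through one binary cut, although finer baseline values are in hand and the protocol itself ties them to response. Adding them kept the type I error in the one null scenario simulated. In the power scenarios it was neutral when the residual effects were zero and helpful otherwise.

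The gain is about 0 to 4 points of power if the residual effects within strata are modest and 5 to 8 points if they are strong (log OR 0.8 to 1.0). These ranges rest on assumed effects, risk-group proportions and, in the table, independence of MAP and grade from the strata and from each other. None of these is given in the protocol. Overlap with the risk stratum would pull the gain towards the lower end.

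The claims that the trial is underpowered, or that the stated model is invalid, are not supported.

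**What to change.** 1. Reconcile the Synopsis with 8.3.1: state whether the stratified CMH test or the logistic model is the primary comparison of Day-28 ORR, and give the other a defined supporting role.
2. Before arm-level outcomes are examined, specify the logistic model in both places as arm + the two stratification factors + logit(MAP) as a continuous term + baseline GVHD grade (III–IV vs lower).
3. Report the standardised (marginal) ORR difference with its 95% CI from that model. The trial is planned on a 20-point difference, and this puts the result on the same scale.
4. If outcomes have already been examined, keep the present model and present the extended one as a labelled sensitivity analysis.

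The cost is a few lines of text and two model terms, with no extra patients or measurements. The downsides are small: the new terms partly overlap with the risk stratum, with about 62 non-responders expected among 178 evaluable patients, and the conditional odds ratio changes scale when covariates are added. The standardised difference resolves the second.

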### 8.3.2. Secondary Analyses

The estimated rates with two-sided 95% confidence intervals (CIs) are used for secondary endpoints (proportion of CR patients and patients who stopped treatment). The ORR on day 28 is calculated with its 95% CI. Kaplan–Meier method is used to estimate the DOR, OS, and DFS, and the log-rank test is used to evaluate the difference between the groups ^[21]^. The cumulative incidence of NRM and relapse is estimated using a competing risk model and compared using the Fine and Gray test. The Cox proportional hazard regression model is used for multivariable regression analysis for OS and DFS. The multivariable regression analysis for NRM is performed using the Fine–Gray proportional hazard regression for competing events. Potential risk factors considered in the regression analysis include primary disease, cytogenetic risk, age and gender of the donor and recipient, graft source, treatment arm, acute GVHD risk, and disease status before transplantation. The cumulative incidence of recurrent acute GVHD is analyzed using the Fine and Gray test in a competing risk framework. The threshold for statistical significance is set at 0.05, and all tests are two-sided. All analyses are carried out using SPSS 22.0 software (IBM Corporation, Armonk, NY, USA) and R version 4.1.2 (www.cran.r-project.org). The treatment-induced differences in OS and DFS will be based on the Cox proportional hazard regression model. The reported treatment difference in NRM and relapse will be based on the multivariate analysis using Fine–Gray proportional hazard regression.

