# 2. STUDY OBJECTIVES AND ENDPOINTS

| Primary Objective | Primary Endpoint |
| --- | --- |
| Compare the efficacy of ruxolitinib in combination with 1mg/kg methylprednisolone versus 2 mg/kg methylprednisolone alone in terms of overall response rate (ORR) at Day 28 in subjects with acute graft-versus-host disease (acute GVHD). | ORR at Day28, defined as the proportion of participants demonstrating a complete response (CR), or partial response (PR) |
| Secondary Objective | Secondary Endpoints |
| Compare additional response and longer-term efficacy outcomes between treatment cohorts. | Durable ORR at Day56, defined as the proportion of patients in each arm whose response on day 28 lasts until day 56 after randomization. |
|  | DOR at Month 6 for responders will be calculated. The DOR is defined from the time of the onset of response to loss of response. Subjects who died or discontinued will be censored at the  death date or the previous assessment. |
|  | Response duration, defined as the time from the first response to the first recurrence/progression of acute GVHD or additional immunosuppressants for GVHD. |
|  | NRM at Month 24, defined as the time from enrollment to death due to any causes other than hematologic disease relapse. |
|  | Cumulative incidence of relapse (CIR) at Month 24, defined as the proportion of subjects whose underlying hematologic disease relapses. |
|  | Disease-free survival (DFS) at Month 24, defined as the time from enrollment to relapse of primary disease or death from any causes, whichever occurred first. |
|  | Failure-free survival (FFS) at Month 24, defined as the time from randomization to disease relapse or progression, non-relapse mortality, or the addition of new therapy for acute GVHD. |
|  | Overall survival (OS) at Month 24, defined as the time from randomization to death due to any causes. |
| Assess the incidence and severity of adverse events (AEs) and serious adverse events. | Clinical safety data (eg, AEs, infections) will be tabulated and listed. |
| Evaluate the use and discontinuation of  corticosteroids. | Average and cumulative corticosteroid dose at Days 365; proportion of subjects who discontinue corticosteroids at Days 56 and 100. |
| Evaluate the use and discontinuation of  immunosuppressive medications. | Proportion of subjects who discontinue immunosuppressive medications at Days 365. |
| Evaluate the incidence of recurrent acute GVHD. | Incidence rate of recurrent acute GVHD through Month 12. |

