## 8.4. Handling of missing data

All randomized participants will be included in the primary analysis of all outcomes. The proportion of missing values on the primary and secondary outcomes would be <10%. Thus, a secondary analysis should be considered using multiple imputations and present best-case/worst-case scenarios if ignoring the missing data is not plausible.

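### Duration of response is tested between arms by log-rank although it exists only in responders, so its p-value is not a randomised comparison; the synopsis does not list that test

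*Protocol*

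**What the plan says.** Section 2 (and the synopsis, in the same terms) lists DOR under the secondary objective of comparing further response and longer-term efficacy between the treatment cohorts. It states that "DOR at Month 6 for responders will be calculated" and that "The DOR is defined from the time of the onset of response to loss of response". On censoring it says "Subjects who died or discontinued will be censored at the" date of death or the preceding assessment.

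Section 8.3.2 gives the method: "Kaplan–Meier method is used to estimate the DOR, OS, and DFS, and the log-rank test is used to evaluate the difference between the groups". It adds that "The threshold for statistical significance is set at 0.05, and all tests are two-sided". Nothing there marks DOR as descriptive.

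The statistical part of the synopsis differs. Its Kaplan–Meier and log-rank list names Day 56 ORR, OS, DFS and FFS, but not DOR, and it places all analyses on the intention-to-treat set.

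Section 2 also has two endpoints that do not condition on having responded: durable ORR at Day 56, a proportion of patients in each arm, and FFS, timed from randomisation.

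**The concern.** OS and DFS have a value for every randomised patient. DOR has one only after a response, and response is what the treatment is meant to change: the sample size rests on 55% against 75% at Day 28. Restricting the comparison to responders gives up the balance that randomisation provides. The ruxolitinib responders may include patients whose counterparts in the control arm did not respond and so are absent from the comparison.

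A difference in DOR can then reflect who responded rather than how long a response lasts on each treatment. It could be reported at the 0.05 level beside OS and DFS as though it had the same standing, and it could point the opposite way from the result in all randomised patients. This is separate from how deaths and discontinuations are censored, because the selection remains even with complete follow-up.

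**Working it through.** **The plan's own figure.** Inputs from Section 8.1: 55% vs 75%, two-sided α = 0.05, power 80%, 10% withdrawal. With pooled variance and no continuity correction:

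n = [1.960·√(2·0.65·0.35) + 0.842·√(0.55·0.45 + 0.75·0.25)]² / 0.20² = (1.322 + 0.555)² / 0.04 ≈ 88.1, so 89 per arm.

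89/0.9 = 98.9, so 99 per arm and 198 in total, which reproduces the plan. No event count or power is stated for DOR.

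**Approximate size of the DOR comparison.** The protocol gives no rate of ever responding, so the Day 28 rates serve as a proxy.

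- Control: 0.55 × 99 ≈ 54 responders.
- Ruxolitinib: 0.75 × 99 ≈ 74 responders.
- If every control responder would also respond on ruxolitinib, 0.20 × 99 ≈ 20 of the 74 (0.20/0.75 = 27%) have no control counterpart.
- Without that assumption, the share of patients who would respond on either treatment could lie anywhere from 0.55 + 0.75 − 1 = 30% to 55%.

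**Illustration.** Let a be the probability that a shared responder is still in response at Month 6 (the same on both arms), and m the probability for an extra responder on ruxolitinib. Both are assumptions.

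- Responders only: ruxolitinib (0.55a + 0.20m)/0.75; control a.
- All randomised: ruxolitinib 0.55a + 0.20m; control 0.55a.

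With a = 0.70:

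| m | Responders only, rux vs control | Difference (points) | All randomised, rux vs control | Difference (points) |
|---|---|---|---|---|
| 0.30 | 59.3% vs 70% | −10.7 | 44.5% vs 38.5% | +6.0 |
| 0.40 | 62.0% vs 70% | −8.0 | 46.5% vs 38.5% | +8.0 |
| 0.50 | 64.7% vs 70% | −5.3 | 48.5% vs 38.5% | +10.0 |
| 0.70 | 70.0% vs 70% | 0 | 52.5% vs 38.5% | +14.0 |
| 0.90 | 75.3% vs 70% | +5.3 | 56.5% vs 38.5% | +18.0 |

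The last row shows the opposite distortion: ruxolitinib appears more durable although no shared responder keeps a response longer on it. The table ignores the short gap between randomisation and onset of response.

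**How often the test would be significant.** Simulation: 99 per arm, 4,000 trials per scenario, exponential loss of response, follow-up cut at 6 months, log-rank in responders. Shared responders lose response by Month 6 with probability 31.2% on both arms. That value is borrowed, as an assumption, from the recurrence rate in the phase I study (Section 1.3).

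| Loss in extra responders | Loss among responders, rux vs control | Log-rank significant for control | All randomised in response, rux vs control |
|---|---|---|---|
| 31.2% | 31.2% vs 31.2% | about 2% | 51.6% vs 37.8% |
| 50% | 36.2% vs 31.2% | 7% | 47.8% vs 37.8% |
| 70% | 41.5% vs 31.2% | 24% | 43.8% vs 37.8% |
| 90% | 46.9% vs 31.2% | 47% | 39.8% vs 37.8% |

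In the 70% scenario, suppose ruxolitinib also truly prolongs response in shared responders (hazard ratio 0.8). The log-rank statistic still points towards control in 79% of trials and is significant for control in 11%.

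**The case against.** Several points on the other side stand.

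- **A reader might infer that the subset is defined by the primary outcome, so that exactly 45% of control and 25% of ruxolitinib patients drop out.** The text does not support this. DOR starts at onset of response and is not limited to Day 28 responders. Someone who responds in week 1 and has lost the response by Day 28 fails the primary endpoint yet belongs in the DOR set. The 55% and 75% are proxies only.
- **A reader might infer that the bias must run against ruxolitinib.** That requires the extra responders to be less durable, and the protocol gives no durability figure for either group. The simulation also shows that a significant result the wrong way is uncommon unless the extra responders do much worse.
- **A reader might infer a direct contradiction with Section 8.4, which says** "All randomized participants will be included in the primary analysis of all outcomes". That sentence belongs to a missing-data rule, and a non-responder's DOR is undefined rather than missing, so it is weak support. The synopsis's general intention-to-treat statement can likewise be read as subject to each endpoint's own definition. The difference between the two log-rank lists remains.
- **Comparisons in all randomised patients already exist.** Durable ORR at Day 56 and FFS limit the harm. They do not give durability at Month 6, since one ends at Day 56 and the other is a Month 24 composite, and they leave the DOR test in place.
- **DOR carries little weight.** It is one of many secondary endpoints, and no power calculation rests on it.

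None of this makes the stated log-rank test a randomised comparison.

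**Conclusion.** The concern holds in this form: Section 8.3.2 states a between-arm test on a group selected after randomisation by an outcome that treatment is expected to affect, and the synopsis does not list that test. The p-value lacks the protection of randomisation whatever the durability rates turn out to be.

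How far it misleads, and in which direction, cannot be determined from the protocol. With a = 0.70 and m from 0.30 to 0.50, the responder-only difference is 5 to 11 points against ruxolitinib while the all-randomised difference is 6 to 10 points in its favour. It is zero when durability is equal, and it reverses when extra responders are the more durable. These figures rest on the Day 28 rates as a proxy, on all control responders being responders on ruxolitinib too, and on assumed durability. The trial's data cannot identify the extra responders, so the assumptions cannot be checked afterwards.

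Severity is minor to moderate.

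**What to change.** 1. In Section 8.3.2, remove DOR from the log-rank sentence. Report it by arm in responders as a descriptive Kaplan–Meier estimate with a 95% CI, and say that it is not a randomised comparison.
2. Reconcile Section 8.3.2 with the synopsis: use the same list of endpoints tested by log-rank in both, and note DOR as an exception to the intention-to-treat statement.
3. Base any between-arm conclusion on durability on all randomised patients, using the existing durable ORR at Day 56 and FFS.
4. If durability at Month 6 is wanted, add the proportion of all randomised patients alive and in response at Month 6 without new GVHD therapy, counting non-responders as not in response. Stratify the test by the two randomisation factors in Section 4.4 (disease status before transplantation and acute GVHD risk). State how patients are counted when haematologic relapse ends their GVHD follow-up, as Section 6.5.2 allows.

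The cost is a few sentences in Section 8.3.2 and the synopsis, plus one in Section 2 if item 4 is adopted. No new data are needed: Section 7.5.1 already schedules GVHD grading at Day 180, and the schedule of assessments has a line for new acute GVHD therapies. The DOR p-value is lost. The sample size stays at 198.
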